## Design and methods

This is a randomized controlled trial to examine the efficacy of a culturally and linguistically tailored behavioral telephone-delivered intervention to increase adherence to physician-recommended assessment and treatment of sleep apnea. Participants will be randomized either to a tailored-telephone intervention (TTI) arm or an attention-control (AC) arm. Approximately 340 black participants at risk for sleep apnea will be randomly assigned to one of the two treatment conditions (170 in each arm). Intervention content for the TTI will be delivered by a trained HE who has experience working with minority populations. The HE has a bachelor’s degree and will receive significant training in sleep medicine, including both basic theories and laboratory-based recording and treatment procedures. She will be supervised throughout the study period by the lead investigator. Assessments will be conducted at baseline, and at 6- and 12-months post-randomization. Participants will receive $10 at baseline and $100 at the 6-month follow-up.

The institutional review boards (IRBs) at SUNY Downstate Medical Center (protocol #09-193) and NYU Langone Medical Center (protocol #13-00182) approved this study prior to implementation.

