### Outcomes

The primary outcome will be adherence to physician-recommended assessment and treatment for sleep apnea. The secondary outcomes will include 1) maintenance of recommended treatment at 6 months and at 12 months; 2) waist circumference; 3) lipid levels; 4) BP; and 5) FPG or HbA1c for those who have a DM diagnosis. Outcomes assessment will be conducted at baseline, and at 6- and 12-months post-randomization.

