### Statistical analysis

To describe the characteristics of the study population, we will use measures of central tendencies and dispersion for continuous data; frequency distributions will be used for categorical data. Chi-square tests will be used to compare categorical data, and ANOVA will be used for continuous data. Relationships between mediators of adherence to recommended sleep apnea assessment and CPAP treatment will be examined using binary multivariate logistic regression analysis. The two main dependent measures will be: adherence to physician-recommended sleep assessment (yes versus no) and adherence to CPAP treatment (yes versus no). Candidate mediators will include sleep apnea knowledge, self-efficacy, readiness, and trust/rapport with the HE. Effects of sociodemographic and clinical factors will be adjusted in those analyses. Repeated-measures MANCOVA will be used to examine differences between baseline and follow-up measures (for example, waist circumference (WC), BP, HDL-C, FBG/HbA1c); age, sex, and sleepiness will be entered as covariates. MANCOVA is a robust technique that incorporates routines to account for heterogeneous variances, serial correlations, and variance inflation [41].

### Hypothesis 1

TTI will lead to higher rates of sleep apnea assessment at 6 months. A comprehensive assessment of sleep apnea will be defined by documentation of an appropriate medical and sleep history by a sleep clinician and a nocturnal polysomnographic study.

#### Analysis for hypothesis 1

Analysis will be performed on an intention-to-treat basis. All participants in the treatment arm will be assumed to have received the full dose of the telephone intervention and all participants in the attention-control arm will be assumed to have received no tailored intervention. Prior to testing for intervention effects, we will verify the comparability of the treatment and control arms with respect to all available demographic and personal data. T-tests and chi-square tests will be used for continuous and categorical variables, respectively. Thus, receipt of sleep apnea assessments within the 6-month period will be a binary outcome, yes or no. We will use logistic regression to estimate the odds associated with receipt of sleep apnea assessment contrasting the two study arms.

### Hypothesis 2

TTI will lead to higher adherence rates to recommended follow-up care (that is, CPAP use (> 4 hours a night for 70% of the nights)) post-diagnosis of sleep apnea.

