#### Analysis for hypothesis 2

The analysis plan is similar to that for hypothesis 1. The focus will be on adherence to recommended CPAP treatment. We will use logistic regression to estimate the likelihood of adhering to prescribed CPAP treatment after a diagnosis of sleep apnea was made.

### Hypothesis 3

Effects of the intervention in maintaining adherence will be sustained 6 months after active interventions and interventions will improve clinical outcome measures (WC, BP, HDL-C, and FPG/HbA1c).

#### Analysis for hypothesis 3

We will test the hypothesis that participants in the intervention arm will sustain gains from the initial interactions with the HE, leading to long-term adherence to recommended treatment and follow-up care. It is routinely recommended that participants with sleep apnea return for a follow-up visit after initiating treatments, during which adherence to treatment plan and improvement in sleep parameters is assessed. In our protocol, clinical outcomes (WC, BP, HDL-C, and FPG/HbA1c) will be ascertained post treatment. The analysis plan to test adherence at 6 months post-randomization is similar as for hypotheses 1 and 2; participants returning for a follow-up visit will be grouped as long-term adherents versus non-adherents. Chi-square tests and logistic regression analyses will be used. Repeated-measures MANCOVA will be employed to examine differences between baseline and post-intervention measures (WC, BP, HDL-C, and FPB/HbA1c). *Post hoc* comparisons between groups will be performed with Bonferroni corrections, where univariate results are significant. As required by assumptions governing the use of ANOVA, and since we expect the dependent variables to be modestly correlated, we will first examine their collinearity. Next, normality of the distribution of each measure will be examined and transformations will be performed for non-gaussian distributions. In exploratory analyses, we will determine whether mixed effect modeling would support ANOVA results.

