### Power and sample size calculations

Data obtained from a random sample of black participants recruited from the MetSO Cohort Study has provided a current estimate of the rate of comprehensive assessment of sleep apnea to be expected in the proposed study. Analysis of the data suggested that 47% of participants referred for sleep assessment would adhere to physician recommendations after exposure to TTI, whereas 35% of those in a control group agreed to undergo a sleep assessment. Thus, this represents the likely rate of adherence expected in our AC group. We propose to achieve an adherence rate of 47% among participants exposed to the TTI.

With an expected 12% increase in the adherence rate associated with the TTI, a standard error of 0.10%, and a sample size of 340, the study will be adequately powered (90%) to detect significant increase in the outcome measures using chi-square tests. The primary study outcome in this project is documented receipt of a sleep apnea assessment. A two-tailed test, with alpha = 0.05, comparing adherence rates of 35% with 47% requires 170 participants per group [42]. The precision estimated in that analysis is the approximate expected precision of study data. Specifically, a difference of 12% would be observed at chi-square = 21.03 with a 95.0% confidence interval of 3% to 20%. With the proposed sample size, the study will have 85% power to achieve a one-standard deviation increase in the odds ratio of adherence attributable to proposed mediators: sleep apnea knowledge, self-efficacy, readiness, and trust/rapport with the HE (expressed as continuous variables).

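### Metabolic outcomes: baseline is analysed as a repeated outcome rather than as a covariate, which costs some precision in the arm comparison (secondary outcomes only)

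*Protocol article*

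**What the plan says.** The general paragraph of the Statistical analysis section states: "Repeated-measures MANCOVA will be used to examine differences between baseline and follow-up measures". It gives waist circumference, blood pressure, HDL-C and glucose or HbA1c as examples and adds that "age, sex, and sleepiness will be entered as covariates". The analysis for hypothesis 3 repeats the model: "Repeated-measures MANCOVA will be employed to examine differences between baseline and post-intervention measures".

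On timing, the Outcomes section says: "Outcomes assessment will be conducted at baseline, and at 6- and 12-months post-randomization". Baseline values are therefore available.

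Two further statements bear on the point. Arms are compared post hoc: "comparisons between groups will be performed with Bonferroni corrections, where univariate results are significant". An alternative model appears only as a supporting check: "In exploratory analyses, we will determine whether mixed effect modeling would support ANOVA results". How that model would treat baseline is not stated.

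No part of the article lists a metabolic measure's own baseline value as a covariate.

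**The concern.** In a repeated-measures model whose visits include baseline, the pre-randomisation value is part of the response. The natural arm effect is then the arm-by-time contrast, which with one follow-up is the difference between arms in mean change. Subtracting the whole baseline value amounts to fixing its regression slope at 1. Where the true slope is smaller, the subtraction adds noise, and any chance baseline imbalance is over-corrected in that particular sample. Putting baseline on the covariate side lets the data set the slope.

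Improvement in the metabolic indices is a stated secondary aim and half of hypothesis 3. An arm effect on them has to work through assessment, diagnosis and CPAP use, and the article expects assessment in 47% of the intervention arm against 35% of controls. Averaged over everyone randomised, the effect is likely to be small. The article claims no power for these outcomes, so avoidable imprecision is worth removing.

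**Working it through.** **Inputs.** 170 participants per arm (Design and methods). Two-sided alpha of 0.05, which the article states for the primary outcome and which I borrow here. The correlation rho between baseline and follow-up is not in the document; I assume 0.4 to 0.9. I also assume equal variances at the visits and complete data. The article gives no power, SD or sample size for the metabolic outcomes, so there is no figure of its own to reproduce on this point.

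**Variances per participant, one follow-up, unit SD.**
- Change score (arm-by-time contrast): 1 + 1 − 2·rho = 2(1 − rho).
- Follow-up adjusted for baseline: 1 − rho² = (1 − rho)(1 + rho).
- Ratio, planned to adjusted: 2/(1 + rho), which exceeds 1 for every rho below 1.

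The direction does not need equal variances. With SDs s0 at baseline and s1 at follow-up, the change-score variance minus the adjusted variance is (s0² + s1² − 2·rho·s0·s1) − s1²(1 − rho²) = (s0 − rho·s1)², which is never negative.

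**Power.** Fix an effect with 80% power after adjustment, so its non-centrality is 1.960 + 0.842 = 2.802. The change-score test then has non-centrality 2.802·√((1 + rho)/2). At rho = 0.6 this is 2.802 × 0.8944 = 2.506; 2.506 − 1.960 = 0.546; power = Φ(0.546) = 71%.

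| rho (assumed) | Variance ratio 2/(1+rho) | Worth per arm, 170(1+rho)/2 | Power of change-score test |
|---|---|---|---|
| 0.4 | 1.43 | 119 | 65% |
| 0.5 | 1.33 | 128 | 68% |
| 0.6 | 1.25 | 136 | 71% |
| 0.7 | 1.18 | 145 | 73% |
| 0.8 | 1.11 | 153 | 76% |
| 0.9 | 1.05 | 162 | 78% |

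A simulation with 170 per arm and 5,000 replicates gave ratios of 1.33, 1.19 and 1.03 at rho 0.5, 0.7 and 0.9, against 1.33, 1.18 and 1.05 from the formula.

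**Two follow-ups averaged, all correlations equal to rho.** The change-score variance is (1 + rho)/2 + 1 − 2·rho and the adjusted variance is (1 + rho)/2 − rho².
- rho 0.4: 0.90/0.54 = 1.67, power 58%.
- rho 0.6: 0.60/0.44 = 1.36, power 67%.
- rho 0.8: 0.30/0.26 = 1.15, power 74%.
- rho 0.9: 0.15/0.14 = 1.07, power 77%.

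**Arm main effect, for comparison.** If the test were instead the arm effect averaged over baseline and one follow-up, the effect would be halved and the variance would be (1 + rho)/2. For the same effect the power would be 34%, 24% and 14% at rho 0.4, 0.6 and 0.8.

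**Sleepiness.** Table 2 marks the Epworth scale at the first and second follow-up but not at baseline. Taken from that scale as scheduled, the named covariate would be measured after randomisation.

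**The case against.** The change-score comparison is a valid test under randomisation, so nothing here is biased on average and the point is one of efficiency. That stands. It does not remove the point, because the better estimator uses data already planned.

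It can also be said that a condensed article leaves model details to the analysis plan. That would answer a complaint about something missing. Here the article states the model family twice and names the covariates, and the objection is to what is stated. The mixed model might well handle baseline properly, but it is exploratory and its treatment of baseline is not given.

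The size is open to challenge, and that challenge largely succeeds. Rho is assumed, and for a stable measure, as waist circumference may be, the loss may be near the 5% end. With three visits, a multivariate arm-by-time test has two degrees of freedom per measure, so the powers above are a guide to the relative loss and not the power of the planned test. They also ignore the Bonferroni correction, which lowers power under either analysis but leaves the variance ratio unchanged. The glucose endpoint is FPG or HbA1c depending on diabetes status, so calculations on the full 340 do not carry over to it.

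A reader might infer that power falls to 34% or below. That requires the arm main effect, averaged over baseline and follow-up, to be the test. The article does not say which contrast is used, and its stated interest in differences between baseline and follow-up points towards a time or arm-by-time contrast.

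**Conclusion.** The point holds as a modest and avoidable loss of precision. The direction is certain for any rho below 1. With one follow-up and rho assumed between 0.4 and 0.9, the stated analysis carries about 43% down to 5% more variance than a baseline-adjusted one, and 80% power becomes about 65% to 78%. With two follow-ups averaged and equal correlations, the excess is about 67% down to 7%. A much larger loss would arise only under a main-effect test that the article does not name.

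The documents do not support reading this as bias in the arm comparison from the handling of baseline, or as a threat to the adherence conclusions: only secondary outcomes are affected. The timing of the sleepiness covariate is a different matter. If treatment changes sleepiness, adjusting for a follow-up score could remove part of the effect being estimated.

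**What to change.** For each metabolic measure, take only the follow-up values as outcomes. Fit arm, visit, arm-by-visit and that measure's own baseline value, together with age and sex. A longitudinal model with a common baseline mean in both arms serves equally well. State that the arm difference at each visit is the quantity of interest, report it adjusted with its 95% confidence interval, and keep the planned Bonferroni correction.

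Keep sleepiness as a covariate only if it is measured before randomisation, and name the instrument. If the Epworth scale is meant, reconcile this with Table 2; if no baseline score exists, drop the covariate and say so.

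The cost is a change of wording in the analysis section, made before outcome data are examined by arm. It needs no new metabolic measurements, visits or participants. With 311 participants already randomised according to the Trial status section, it is a cheap way to gain precision.

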The primary aim of this on-going randomized trial is to assess the efficacy of a culturally and linguistically tailored telephone-delivered intervention to increase adherence to physician-recommended assessment and treatment of sleep apnea. The secondary aims are to: 1) evaluate the maintenance of intervention effects on adherence at 6 months post-randomization; and 2) assess treatment effects on indices of the metabolic syndrome (waist circumference, blood pressure (BP), lipid levels and fasting plasma glucose (FPG) or hemoglobin (HbA1c) for those who have a DM diagnosis). There are four main hypotheses for this study: 1) participants will show greater adherence to physician-recommended polysomnographic sleep apnea evaluation during follow-up assessment; 2) participants will show greater adherence to CPAP treatment during follow-up assessment; 3) effects of the intervention on adherence rates will be maintained 6 months after discontinuing active interventions, and treatments will improve indexes of the metabolic syndrome; and 4) participants’ knowledge about sleep, self-efficacy, readiness, and trust/rapport with the health educator (HE) will mediate intervention effects on study outcomes. The study is registered in clinicaltrials.gov.

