### Follow-up procedures

Participants will be instructed that appropriate management of their condition may require attending approximately three clinic visits at the sleep center; the number of visits will vary based on the participants’ diagnosis. During the first visit to the sleep center, participants will have a consultation with the sleep specialist, and complete questionnaires. The sleep specialist will conduct an overview of the participant’s sleep history, and medical history including BP, blood glucose and other health behaviors (for example, regularity of physical examinations, cholesterol screening, smoking and drinking habits, and exercise habits) will be assessed. This initial consultation will also provide participants with another opportunity to ask any questions pertaining to the study procedures and to help participants feel comfortable with the testing environment. Upon diagnosis of sleep apnea, participants will complete a follow-up visit that will include an overnight CPAP titration study. Participants will receive additional information on how to use the device and participants will be reminded that the HE will be available to answer any further questions.

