### Data safety and monitoring

In compliance with the National Institutes of Health regulations, an internal data and safety monitoring committee has been developed. The purpose of the committee is to ensure the safety of participants and the validity and integrity of the data. The committee will meet once per year to monitor the overall conduct of the study. In addition, all participants will be subject to a chart audit and participants will undergo physical exams before and after the intervention. During both visits, participants will be asked to bring bottles of any medications they are currently taking, including statins, antihypertensive, antihyperglycemic, and sleep medications (prescribed and/or over the counter). Trained RAs will note each medication, its name, drug class, and the doses at baseline. During follow-up visits, the RAs will note if there are any changes to any of the medications noted at the previous visit and if a new medication has been added. Participants will be monitored during the course of data acquisition and any health concerns that may arise will be addressed, particularly among participants with no identifiable primary-care physicians, in which referrals will be made to primary-care clinics.

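### Hypothesis 3 reads metabolic change as an effect of sleep apnoea treatment, but the recorded changes in blood pressure, lipid and glucose drugs have no stated role in the analysis

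*Protocol article*

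**What the plan says.** The Statistical analysis section of the protocol article states: "Repeated-measures MANCOVA will be used to examine differences between baseline and follow-up measures". Its examples are waist circumference, blood pressure, HDL-C and fasting glucose or HbA1c, and for this model "age, sex, and sleepiness will be entered as covariates". The paragraph headed Analysis for hypothesis 3 returns to the same model: "Repeated-measures MANCOVA will be employed to examine differences between baseline and post-intervention measures". It adds Bonferroni-corrected post hoc comparisons, checks of collinearity and normality, and an exploratory mixed model. Neither place mentions medication.

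The section Data safety and monitoring describes a careful drug record covering statins, antihypertensive, glucose-lowering and sleep medication. "Trained RAs will note each medication, its name, drug class, and the doses at baseline". Later in the trial, "the RAs will note if there are any changes to any of the medications noted at the previous visit and if a new medication has" since come into use. No analytic use of this record is stated.

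The third main hypothesis in the Background expects that "treatments will improve indexes of the metabolic syndrome". Follow-up procedures says that the first sleep-centre visit covers "medical history including BP, blood glucose and other health behaviors".

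**The concern.** Three of the secondary outcomes (blood pressure, lipids, glucose) are the direct targets of drugs that many participants probably take. Table 1 gives 73.1% hypertension, 50.2% diabetes and 48.4% dyslipidaemia in the source registry. These figures are diagnoses, not drug use, but they make background treatment likely to be common. Drug treatment may change during the trial.

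The intervention aims to bring more people to a sleep specialist whose consultation takes in blood pressure and blood glucose. If that contact leads to more drug starts or increases in the intervention arm, part of any metabolic improvement is a drug effect. If CPAP lowers blood pressure and fewer intervention participants then have their drugs increased, a real benefit is hidden. At stake is the interpretation of Hypothesis 3. The primary outcome is not affected.

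**Working it through.** The article gives no effect size, standard deviation or power for the metabolic outcomes, so there is no figure to reproduce. The check is first a comparison of text and then an illustration on assumed inputs.

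**Text**

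1. The covariate list for the MANCOVA names three variables. The wording that marks examples applies to the outcomes, not to the covariates.
2. The sentence promising adjustment for sociodemographic and clinical factors refers back to the logistic analyses of mediators and adherence. It does not reach the MANCOVA.
3. The check of arm comparability under Analysis for hypothesis 1 comes before the tests of effect. It can show an imbalance at entry but says nothing about later drug changes.
4. Nowhere is medication a covariate, a stratum, an event with a stated handling, or a sensitivity analysis for these outcomes.

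**Illustration**

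Inputs: 170 per arm (Power and sample size calculations) and two-sided alpha 0.05. Assumed, because the documents give no values: a drug change worth e = 5 to 10 mmHg systolic; a between-arm difference d = 5 to 20 percentage points in the share with such a change; SD = 10 to 20 mmHg for the analysed value.

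Formulas:
- shift in the arm difference = e × d
- SE = SD × √(2/170) = SD × 0.1085, which is 1.08, 1.63 and 2.17 mmHg for SD 10, 15 and 20
- chance of a significant result with no effect of sleep apnoea treatment = Φ(shift/SE − 1.96) + Φ(−shift/SE − 1.96)

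| e (mmHg) | d (points) | shift (mmHg) | SD 10 | SD 15 | SD 20 |
|---|---|---|---|---|---|
| 5 | 5 | 0.25 | 5.6% | 5.3% | 5.2% |
| 5 | 10 | 0.5 | 7.5% | 6.1% | 5.6% |
| 10 | 10 | 1.0 | 15.2% | 9.4% | 7.5% |
| 10 | 20 | 2.0 | 45.4% | 23.3% | 15.2% |

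Masking: take a true arm difference of 3 mmHg at SD 15 and count significant results in the direction of benefit. Power is 45% with no masking. It is 34%, 23% and 9% when drug changes offset 0.5, 1 and 2 mmHg.

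**The case against.** The strongest reply is that randomisation balances baseline drugs in expectation, and that a comparison by assigned arm validly estimates what the telephone intervention does, downstream drug changes included. That stands. The statement of Hypothesis 3 in the analysis section credits the interventions, and for that claim nothing is broken. The difficulty is confined to the Background wording that credits treatment, and to any before-after contrast, which randomisation does not protect.

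The second reply is that the evidence for an arm imbalance is indirect. That also stands. Referral to primary care under Data safety and monitoring applies to everyone. Other health topics appear only as a category in the health educator's call log. Follow-up procedures does not mention prescribing, and controls who attend get the same visit. Controls also receive up to 10 calls. With the planned assessment rates of 47% and 35%, and an equal chance of a drug change per attendee in each arm, attendance alone gives an imbalance of at most 0.47 − 0.35 = 12 points, and only if every extra attendee had a change. The top of the assumed range would need a further route.

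The third reply is that drug-change tables and sensitivity analyses belong in an analysis plan that is not shown. This carries some weight, but the article itself names the model and its covariates for these outcomes, so the omission can be judged on its text.

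A reader might also infer that the 12-point gain limits the arm-level effect of sleep apnoea treatment to 0.12 of the individual CPAP effect, so that a small drug imbalance would swamp it. The documents do not support this. The 12 points concern receipt of an assessment, whereas Phase II and Hypothesis 2 also aim to raise CPAP use among everyone diagnosed. If all those assessed were diagnosed and adherence were 70% against 30% (assumptions), the difference in CPAP use would be 0.47 × 0.70 − 0.35 × 0.30 = 0.329 − 0.105 = 0.224, or 22.4 points.

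**Conclusion.** The point holds in limited form. The trial records drug data that bear directly on blood pressure, lipids and glucose, yet the stated analysis does not use them. A difference in these outcomes therefore cannot be assigned to sleep apnoea treatment rather than to drug changes. It remains valid as a total effect of the intervention, and it would be wrong to conclude that the Hypothesis 3 comparison is invalid.

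The size is unknown because the documents say nothing about how far drug changes will differ by arm. On the assumptions shown, the consequence ranges from negligible (5.2% against a nominal 5%) to material (23% at a 2 mmHg shift and SD 15, and 45% at SD 10). The distortion can go in either direction. Waist circumference is much less exposed. These are secondary outcomes, so the change is worth making but does not affect the trial's main conclusion.

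**What to change.** - Add baseline use of the matching drug class as a covariate: antihypertensives for blood pressure, lipid-lowering drugs for lipids, glucose-lowering drugs for FPG/HbA1c. The gain is mainly precision; this does not deal with later changes.
- Do not enter post-baseline drug changes as covariates, since they can be consequences of the arm or of the outcome itself.
- Report drug starts, increases and reductions by arm beside each outcome.
- Prespecify one sensitivity analysis per outcome that shifts follow-up values recorded after a drug change by an amount varied over a stated range.
- Word the main Hypothesis 3 result as the total effect of the intervention. Describe it as an effect of sleep apnoea treatment only with the drug-change data as a caveat. Agreement of the sensitivity analysis would not itself show that CPAP caused the difference, so attribution should not depend on it.

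The cost is analysis wording, coding of medication data already collected, a few more covariates and one extra table for secondary outcomes. Neither data collection nor clinical care changes.
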